### Statistical analysis

2.12

#### Efficacy assessment

2.12.1

The baseline characteristics will be analyzed by a *t* test for continuous variables or a chi-square test (Fisher's exact test will be conducted when the expected value is < 5) for categorical variables. If the normality assumption is not satisfied for the continuous variables, Mann-Whitney *U* test will be used. The last observation carried forward (LOCF) method will be used for missing values. For the efficacy assessment, an independent *t*-test will be conducted to compare the mean differences between the baseline and visit 4 for the 2 groups. In addition, paired *t*-test will be conducted to see intergroup changes between baseline and visit 4. Statistical analyses for efficacy will be conducted for both the ITT (intention-to treat, all randomized participants who administered at least single dose of investigational product), and PP (per-protocol, participants who completed the study without any major protocol deviations). The ITT analyses will be the primary analyses and PP analysis will be for reference. If the *P* value is <.05, the result will be considered as statistically significant. There is no plan for interim analysis.

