### Participants

2.2

The inclusion criteria are as follows:20 years or older;patients undergone segmentectomy or lobectomy for lung cancer within 1 month;patients who do not or poorly respond to one week administration of common antitussive agents;Eastern Cooperative Oncology Group (ECOG) performance status 0 to 2;participants who are willing and able to give informed consent for participation in the study.

The exclusion criteria are as follows:patients undergoing adjuvant chemotherapy;patients who have been diagnosed with acute respiratory disease within 1 month;patients who have been diagnosed with bronchial asthma or bronchiectasis within 1 year;patients taking angiotensin converting enzyme inhibitor;patients diagnosed pneumonia with a positive chest x-ray;patients with infection suspected to the cause of cough in sputum cultures;patients with pseudoaldosteronism;participants who have known prior hypersensitivity to any investigational product component;patient with acute or chronic infections requiring treatment (active hepatitis A, B, and C viruses, human immunodeficiency virus, tuberculosis);pregnant or lactating females;women of childbearing potential;patients who do not agrees to use effective means of contraception and not to donate sperm during the trial and up to 1 month after final administration;patient who participated other clinical trials of medicine or medical devices within 1 month; andindividuals who are judged inappropriate for the study by investigator

The withdrawal criteria are as follows, and the reasons of the withdrawal will be clarified in the case report forms (CRFs):participants who do not follow the instructions of investigators;occurrence of significant protocol violations;occurrence of a serious adverse event (AE);investigator's decision to terminate the process for the sake of the participant's health; andparticipant's withdrawal of consent

The participants who are withdrawn from the study after allocation will be followed for outcome measurements as far as possible.

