### Sample size

2.4

Sample size calculation was conducted based on previous study that reported efficacy of MMDT on prolonged cough after lung cancer surgery.^[7]^ There was no study evaluated efficacy of MMDT using Leicester Cough Questionnaire (LCQ) in patients with lung cancer, thus, the changes of Short-From 36 (SF-36) score of the previous study were transformed to LCQ score. The mean differences of LCQ scores were hypothesized to be 8.40 and 5.52 in MMDT group and placebo group, respectively, and the standard deviation was hypothesized to be 3.45. The following formula was used to calculate the sample size. The calculation was performed using 95% power, and a 5% significance level 
[figure not shown]

Considering a drop-out rate of 20%, the needed sample size is approximately 48 participants for each group. Therefore, a total of 96 participants are needed for the present study.

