### Primary outcome measurement

2.9

The primary outcome in the present study is the change in the LCQ score between the baseline (Visit 2) and after the treatment (Visit 4). The LCQ is a valid, repeatable cough-specific quality of life questionnaire consists of 19 items, each rated on a 7-point Likert scale.^[17]^ Korean version of the LCQ also has been validated its concurrent validation, internal consistency, repeatability, and responsiveness.^[18]^ The total score of LCQ is 3 to 21, and a higher score means a better quality of life. The LCQ will be measured at visit 2, 3, and 4.

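### LOCF in the primary ITT analysis biases the LCQ difference when drop-out differs by arm and shrinks it when drop-out is equal; power can fall well below 95%, but need not

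*Protocol article*

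**What the plan says.** All references are to the protocol article.

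- Section 2.12.1 (Efficacy assessment) fixes the method for missing data: "The last observation carried forward (LOCF) method will be used for missing values". It names no other method.
- The same section sets the primary test: "an independent *t*-test will be conducted to compare the mean differences between the baseline and visit 4 for the 2 groups". It also ranks the analysis sets: "The ITT analyses will be the primary analyses and PP analysis will be for reference".
- Section 2.9 (Primary outcome measurement) limits what can be carried forward: "The LCQ will be measured at visit 2, 3, and 4". Visit 2 is the baseline.
- Section 2.4 (Sample size) expects large gains in both arms: "The mean differences of LCQ scores were hypothesized to be 8.40 and 5.52 in MMDT group and placebo group, respectively". It assumes an SD of 3.45 for the change, then allows for losses: "Considering a drop-out rate of 20%, the needed sample size is approximately 48 participants for each group".
- Section 2.2 (Participants) plans to collect data after withdrawal: "The participants who are withdrawn from the study after allocation will be followed for outcome measurements as far as possible".

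**The concern.** Carrying the last value forward assumes that a patient's LCQ would not have changed after the last visit attended. The plan's own figures say the opposite, since both arms are expected to gain several points in 4 weeks. A patient lost before Visit 3 is entered with a change of zero, and one lost later keeps the Visit 3 score. Each filled value is then treated as if it had been observed.

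Each arm's mean is pulled down in proportion to its losses, even when leaving has nothing to do with cough. If placebo loses more patients, the bias favours MMDT. If MMDT loses more, a real effect is hidden. If losses are equal, a real effect is diluted. LOCF therefore cannot be defended as conservative here, and it sits in the single primary comparison.

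**Working it through.** **1. The plan's own figure.** Inputs from section 2.4: difference 8.40 − 5.52 = 2.88, SD 3.45, 5% significance level (taken as two-sided), 95% power.

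n per arm = 2 × 3.45² × (1.960 + 1.645)² / 2.88² = 37.3, rounded up to 38. With 20% drop-out, 38 / 0.8 = 47.5, rounded up to 48 per arm, 96 in total. This reproduces the plan. It treats drop-outs as lost, whereas the LOCF analysis keeps them with a carried value.

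**2. Model for LOCF.** Let q be the drop-out proportion in an arm, μ its expected final gain, and f the fraction of that gain present in the carried value (f = 0 means baseline is carried). Drop-out is at random, and carried values have SD f × 3.45.

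- Arm mean under LOCF: μ × [1 − q(1 − f)]
- Arm variance: (1 − q) × 3.45² + q × (f × 3.45)² + q(1 − q) × [(1 − f)μ]²
- Bias of the difference: (1 − f) × (q_placebo × μ_placebo − q_MMDT × μ_MMDT)
- Power ≈ Φ(difference / SE − 1.96), with SE = √[(sum of the two variances) / 48]

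The values of q by arm and of f are assumptions. The article gives one overall rate of 20%, and the visit schedule is in a table that is not shown.

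**3. No true effect, both arms gaining 5.52.** With 10% MMDT v 30% placebo drop-out and f = 0, the arm means are 5.52 × 0.90 = 4.97 and 5.52 × 0.70 = 3.86, a false difference of 1.10. With f = 0.75 it is 5.52 × 0.20 × 0.25 = 0.28. With equal drop-out it is zero.

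**4. True difference 2.88, drop-out 30% MMDT v 10% placebo, f = 0.** The means are 8.40 × 0.70 = 5.88 and 5.52 × 0.90 = 4.97, a difference of 0.91. The SDs are 4.81 and 3.67, so SE = 0.873. Then 0.912 / 0.873 − 1.96 = −0.92, and power is 18%.

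**5. True difference 2.88, equal 20%, f = 0.** The means are 6.72 and 4.42, a difference of 2.30. The SDs are 4.56 and 3.79, so SE = 0.857. Then 2.304 / 0.857 − 1.96 = 0.73, and power is 77% (75% to 76% in simulated t-tests).

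**6. Range over f.** Type I error is two-sided, from simulated t-tests (at least 20,000 trials per case). Power is from the formula.

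| Drop-out, MMDT v placebo | Quantity | f = 0 | f = 0.5 | f = 0.75 |
|---|---|---|---|---|
| No effect, 10% v 30% | bias | 1.10 | 0.55 | 0.28 |
| | type I error | 30% | 12% to 13% | 7% |
| No effect, 15% v 25% | bias | 0.55 | 0.28 | 0.14 |
| | type I error | 11% | 7% | 5% to 6% |
| No effect, 20% v 20% | type I error | 5% | 5% | 5% |
| Effect 2.88, 30% v 10% | estimate | 0.91 | 1.90 | 2.39 |
| | power | 18% | 75% | 93% |
| Effect 2.88, 25% v 15% | estimate | 1.61 | 2.24 | 2.56 |
| | power | 46% | 88% | 96% |
| Effect 2.88, 20% v 20% | estimate | 2.30 | 2.59 | 2.74 |
| | power | 77% | 95% | 98% |
| Effect 2.88, 10% v 30% | estimate | 3.70 | 3.29 | 3.08 |
| | power | 99.5% | 99.7% | 99.4% |

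In the last case power is high only because the estimate is biased upwards. A larger Visit 3 SD (about 2.6) at f = 0.5 lowers the power slightly, to 94% at equal 20% and 72% at 30% v 10%.

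With a true effect, the bias cancels only if 8.40 × q_MMDT = 5.52 × q_placebo, for example 15% v 22.8%. Nothing in the plan would bring that about.

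**7. Comparison without carried values.** If drop-out is uninformative, analysing only the observed patients gives 95.5% power with 20% lost in each arm, and 95.2% at 10% v 30% in either direction, without bias.

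**The case against.** **Size.** The strongest reply is that the size rests on inputs the article does not give. No Visit 3 level is stated, and f = 0 requires every drop-out to leave before Visit 3. That stands, and it is why the result is shown as a range. If three quarters of the gain is reached by Visit 3, the harm is small in most rows.

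**Unequal drop-out.** Nothing predicts a 20-point gap between arms. If both truly lose 20%, a gap that large arises by chance in about 1.5% of trials, and type I error stays at 5%. So inflation needs a systematic difference between arms. The plan's rules make one possible: withdrawal for serious adverse events could fall more on the active arm, and the ban on other cough treatment could drive more placebo patients out. Both are inference.

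**Follow-up after withdrawal.** Section 2.2 would reduce the missing data. With 10% truly missing in each arm, power is 90% (f = 0) to 97% (f = 0.5). But the follow-up is promised only as far as possible, and section 2.12.1 does not say that scores so collected are used.

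**Stronger readings.** A reader might infer that the planned 95% power is lost. The documents do not support this: at equal 20% drop-out, power is about 95% at f = 0.5 and 98% at f = 0.75. A reader might also infer that section 2.4 is wrong or that its power should be restated. It reproduces exactly, and a restated power would write an assumed Visit 3 level into the protocol. Finally, LOCF alone does not inflate type I error when drop-out is equal.

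**Condensed article.** Detailed model terms and further sensitivity analyses may be in a document not shown, and their absence is no fault. The choice of LOCF, however, is stated and open to comment.

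**Conclusion.** The point holds in conditional form. LOCF is a poor primary method in a trial that expects both arms to improve strongly, because it biases the contrast in either direction when losses differ and attenuates a true effect when they are equal.

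Across f from 0 to 0.75, with 48 per arm and random drop-out:

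- type I error is 30% to 7% at 10% v 30%, and 11% to about 6% at 15% v 25%;
- power is 18% to 93% at 30% v 10%;
- power is 75% to 98% at equal 20%, with the estimate at 2.3 to 2.7 instead of 2.88.

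The direction follows from the plan's own figures. The size depends on the assumed drop-out split, its timing and the Visit 3 level, and it shrinks if follow-up after withdrawal succeeds.

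**What to change.** In section 2.12.1:

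- Replace LOCF as the primary method with a likelihood-based repeated-measures model of LCQ change at Visits 3 and 4, adjusted for baseline LCQ, and take the Visit 4 treatment contrast. Multiple imputation by arm followed by ANCOVA is an acceptable alternative.
- State that the Visit 4 LCQ of withdrawn participants is used wherever it was collected.
- Keep LOCF only as a sensitivity analysis.

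Leave the sample size and stated power in section 2.4 unchanged.

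The cost is a change of wording, with no new visits or data, since Visit 3 is already measured. The analysis becomes slightly more complex to run and report, and it relies on a missing-at-random assumption. The change should be made before unblinding, so that it cannot look driven by the data.

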### Randomization and allocation

2.5

The enrolled participants will be randomized using random numbers generated by computer at an independent centre, Institute of Safety, Efficacy and Effectiveness Evaluation for Korean Medicine (ISEE). The study participants will be assigned to one of 2 groups with a 1:1 allocation ratio in blocks of 4 by investigators in each trial institutions. The randomization table will be kept in an opaque sealed envelope and maintained by the ISEE during the trial period. The randomization table should be opened according to Standard Operating Procedures (SOPs).

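### The efficacy test is an unadjusted t-test on change; using the Visit 2 score as a covariate would be as valid, generally more precise and would cost nothing

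*Protocol article*

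**What the plan says.** Section 2.9 of the protocol article defines the primary outcome as the change in Leicester Cough Questionnaire (LCQ) score from Visit 2 to Visit 4, and adds: "The LCQ will be measured at visit 2, 3, and 4". The scale runs from 3 to 21.

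Section 2.12.1 names the test, an independent t-test that "will be conducted to compare the mean differences between the baseline and visit 4 for the 2 groups". No covariate or site term is mentioned. Baseline characteristics are compared between groups by significance tests, and nothing in the efficacy analysis follows from those tests. The primary population is all randomised participants who took at least one dose, with last observation carried forward.

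Section 2.4 sizes the trial on the same comparison: "The mean differences of LCQ scores were hypothesized to be 8.40 and 5.52 in MMDT group and placebo group, respectively". The SD assumed there is 3.45.

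Section 2.5 says that participants are assigned "with a 1:1 allocation ratio in blocks of 4 by investigators in each trial institutions". Five hospitals take part.

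**The concern.** The choice of test is stated outright, so it is not a detail that the article leaves to a fuller document. A change score amounts to a regression on baseline with the slope set to 1. The slope in the data is usually lower: on a bounded scale, patients who start worse have more room to improve, so change tends to be negatively related to the starting value. Two things follow if the slope is not 1.

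- **Precision.** The t-test carries variance that the baseline score could remove.
- **Chance imbalance.** If the arms differ at Visit 2, the estimate moves with that difference. Testing baseline variables for significance does not remove the shift.

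The cough VAS and the YDS are also measured at Visit 2 and analysed as changes, so the same applies to them.

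This matters more because the assumed effect is uncertain. Section 2.4 says that no earlier study of this medicine had used the LCQ in lung cancer patients and that the figures were converted from SF-36 changes. Section 3 describes the earlier study as small and single-centre.

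**Working it through.** **Inputs from the article.** Difference in mean change 8.40 − 5.52 = 2.88; SD 3.45, read as the SD of the change; power 95%; alpha 5%, with sidedness not stated; dropout 20%; 48 per arm.

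**Inputs assumed.** The correlation rho between Visit 2 and Visit 4 LCQ (0.3 to 0.9) and the ratio k of the Visit 4 SD to the Visit 2 SD. The article gives neither.

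**Step 1: the plan's own figure.** n = 2 × (3.45 × (1.960 + 1.645) / 2.88)² = 37.3, so 38 per arm. Then 38 / 0.80 = 47.5, so 48 per arm and 96 in total. This matches, with a two-sided test; a one-sided test would give 32 per arm before dropout. The sample size is consistent with the unadjusted test.

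**Step 2: variance.** Let s be the Visit 2 SD.

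- Variance of change: s²(1 + k² − 2·rho·k).
- ANCOVA residual variance: k²s²(1 − rho²).
- The difference is s²(1 − rho·k)². It is never negative, and it is zero only when the true slope rho·k equals 1.
- With k = 1 the ratio of ANCOVA to change-score variance is (1 + rho)/2.

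**Step 3: results with k = 1.** Power is from the noncentral t distribution, two-sided 5%, with 38 per arm. The interval half-width is 1.96 × SD × √(2/38).

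| Analysis | Variance saved | SD | 95% CI half-width | Power at 2.88 | Power at 2.0 (assumed) |
|---|---|---|---|---|---|
| t-test on change | – | 3.45 | 1.55 | 94.9% | 70% |
| ANCOVA, rho 0.3 | 35% | 2.78 | 1.25 | 99.4% | 87% |
| ANCOVA, rho 0.5 | 25% | 2.99 | 1.34 | 98.6% | 82% |
| ANCOVA, rho 0.7 | 15% | 3.18 | 1.43 | 97.4% | 77% |
| ANCOVA, rho 0.9 | 5% | 3.36 | 1.51 | 95.8% | 73% |

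Removing five further degrees of freedom (one for baseline, four for site) changes these powers by at most 0.1 percentage point.

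**Step 4: unequal SDs.** With k = 1.5 the saving is 13%, 4% and 0.2% at rho 0.3, 0.5 and 0.7, because rho·k is then 0.45, 0.75 and 1.05. At rho 0.9 the slope would be 1.35 and the saving 22%; the change score would then under-correct. With k = 0.8 and rho 0.5 the saving is 43%.

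**Step 5: chance imbalance with k = 1.** If the medicine arm starts D points higher, the expected change-score estimate moves by −(1 − rho)·D. The implied Visit 2 SD is 3.45 / √(2(1 − rho)), and one standard error of the baseline difference at 38 per arm is that SD × √(2/38).

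| rho | Visit 2 SD | 1 SE of baseline difference | Shift in estimate |
|---|---|---|---|
| 0.3 | 2.92 | 0.67 | 0.47 |
| 0.5 | 3.45 | 0.79 | 0.40 |
| 0.7 | 4.45 | 1.02 | 0.31 |
| 0.9 | 7.71 | 1.77 | 0.18 |

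These shifts compare with a planned effect of 2.88.

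**Step 6: site, if the blocks are within institution.** Five sites of 16 patients, with blocks of 4 within site, were simulated for assumed intraclass correlations of 0.05, 0.10 and 0.20. The t-test's type I error was 4.6%, 3.9% and 3.2%, against about 5% with a site term. Power lost by omitting site was about 0.2 to 1.0 percentage point.

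**The case against.** The strongest reply is that nothing here is wrong in the strict sense. Averaged over randomisation, the t-test on change is unbiased. It matches the endpoint in section 2.9 and the calculation in section 2.4, and the trial is planned at 95% power. All of this stands.

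Three further objections also hold in part.

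- **Size of the gain.** The 2.0-point effect is not in the article. At the planned 2.88 points the gain is only about 1 to 4.5 percentage points. The primary population with values carried forward could also reach 48 per arm. Nominal power is then 98.2% unadjusted at 2.88 points, against 98.6% to 99.9% adjusted, and 80% unadjusted at 2.0 points.
- **Assumptions.** The 35% to 5% saving is one scenario. At rho 0.5 or 0.7 it nearly vanishes if scores are 1.5 times as variable at Visit 4.
- **Site.** The wording of section 2.5 may say only who makes the assignment.

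A reader might infer that the test ignores baseline and leaves imbalance uncorrected. It does not: every Visit 4 score has its own baseline subtracted, so imbalance is corrected with a slope that may be wrong. A reader might also take randomisation to be stratified by hospital, or the t-test to inflate false positives. The article does not state the first. If it is true, leaving site out makes the test slightly conservative, which is the opposite of the second.

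What the reply does not answer is why a covariate already collected should go unused when the effect size was converted from another instrument.

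**Conclusion.** The concern holds as a matter of efficiency and robustness. Section 2.12.1 fixes a valid test that is generally less precise than ANCOVA and that over-corrects chance baseline differences when the true slope is below 1.

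At the protocol's own effect the benefit is modest, because planned power is already about 95%. It becomes material if the true effect is smaller: at an assumed 2.0 points and 38 per arm, the gain is 17, 12, 7 or 2 percentage points at rho 0.3, 0.5, 0.7 or 0.9. Narrower intervals and protection against imbalance come in either case.

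The direction is secure, since ANCOVA's residual variance cannot exceed that of the change score apart from the negligible cost in degrees of freedom. The size is not secure: it rests on an unstated rho and on equal SDs at the two visits. Site is a minor part of the point and depends on a reading of section 2.5 that is fair but not confirmed by the text.

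**What to change.** In section 2.12.1, before unblinding:

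1. Make the primary analysis an ANCOVA of Visit 4 LCQ (or, equivalently for the treatment effect, of the change) on treatment and Visit 2 LCQ. Report the adjusted difference with its 95% confidence interval.
2. Analyse the cough VAS and the YDS in the same way, each with its own Visit 2 value.
3. State in section 2.5 whether the blocks of 4 are formed within institution. If they are, add site as a factor.
4. Keep the independent t-test on change as a supportive analysis.

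The cost is a sentence or two of text, one degree of freedom for baseline and four for site. No new data are needed, and the sample size stays at 96.

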#### Safety assessment

2.12.2

All the safety related variables such as vital signs and laboratory test results will be compared between MMDT group and placebo group at every visit. We will check whether there is a significant difference between the 2 groups by *t*-test and whether there is a change beyond the normal range. The incidence of AEs will be compared by chi-square test. The statistical analyses for safety will be conducted by ITT analyses.

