### Safety outcomes

2.11

All variables related to the participants’ safety including vital signs, physical examination, hematologic test, biochemical test, and urine test will be documented on the CRFs at every visit. Any AEs that occur after taking investigational drug will be documented on the CRFs. If the AE is severe and related to the investigational product, the participant will be withdrawn from the study, and the appropriate treatment and reimbursement will be provided to them.

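### The by-visit t-tests for vital signs and laboratory values make no stated use of the Visit 2 baseline, take in pre-treatment visits if read literally, and are insensitive to a few large individual abnormalities

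*Protocol article*

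**What the plan says.** Section 2.12.2 (Safety assessment) states that vital signs and "laboratory test results will be compared between MMDT group and placebo group at every visit". The analysts will check "whether there is a significant difference between the 2 groups by *t*-test and whether there is a change beyond the normal range". It adds that "The incidence of AEs will be compared by chi-square test" and that "The statistical analyses for safety will be conducted by ITT analyses".

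Other sections that bear on this:

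- 2.11 (Safety outcomes): vital signs, examination and laboratory tests are recorded at each visit, so pre-treatment values exist. It also says: "If the AE is severe and related to the investigational product, the participant will be withdrawn from the study".
- 2.9 (Primary outcome measurement): Visit 2 is the baseline and Visit 4 is after treatment. Section 2.1 gives four visits in all.
- 2.2 (Participants): a serious adverse event is a withdrawal criterion. Outcome measurement is to continue in withdrawn participants where it can.
- 2.12.1 (Efficacy assessment): the efficacy t-test compares change from baseline to Visit 4. "The last observation carried forward (LOCF) method will be used for missing values" stands in this section, as does the definition of ITT: "all randomized participants who administered at least single dose of investigational product".

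**The concern.** Safety is half of the stated aim, and the t-test is the only between-arm test named for laboratory and vital-sign values. As written it has three weaknesses.

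1. It covers every visit. Visit 2 is the baseline and Visit 1 precedes it, so both come before treatment. A difference between randomised arms at those visits can only be chance.
2. At Visits 3 and 4 it makes no stated use of the participant's own Visit 2 value, whereas the efficacy test does use baseline. Where repeated values correlate, this discards precision at no saving.
3. A mean at a fixed visit responds little to a few participants with large abnormalities, which is how laboratory harm often appears. Participants withdrawn for a serious event, or for a severe and related one, may have no value at a later visit, which would weaken the comparison further.

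What is at stake is a laboratory comparison that reports no difference because it had little chance of showing one.

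**Working it through.** **Arm size.** From 2.4: difference 8.40 − 5.52 = 2.88, SD 3.45, 95% power, 5% two-sided. n = 2(1.960 + 1.645)² × 3.45² / 2.88² = 37.3, so 38 per arm. Allowing 20% drop-out, 38 / 0.8 = 47.5, so 48. The plan's figure reproduces. The plan gives no figure for the safety tests, so everything below is an illustration at 48 per arm on assumed shifts and correlations.

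**Pre-treatment visits.** Each test has a 5% chance of significance with no possible treatment effect. For one variable at Visits 1 and 2, the chance of at least one such result lies between 5% (values perfectly correlated) and 1 − 0.95² = 9.75% (independent).

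**Uniform shift, use of baseline.** Assume a true shift of 0.5 SD, with correlation ρ between the Visit 2 value and the later value. Adjustment leaves a residual SD of √(1 − ρ²). The non-centrality is 0.5 × √(48/2) / √(1 − ρ²) = 2.449 / √(1 − ρ²), and the critical t on 94 df is 1.986.

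| Analysis | Residual SD | Non-centrality | Power |
|---|---|---|---|
| Unadjusted | 1.000 | 2.449 | 68% |
| Adjusted, ρ = 0.5 | 0.866 | 2.828 | 80% |
| Adjusted, ρ = 0.7 | 0.714 | 3.430 | 92% |
| Adjusted, ρ = 0.8 | 0.600 | 4.082 | 98% |

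At ρ = 0.7 the adjustment is worth as much as raising the arms from 48 to 48 / 0.51 = 94.

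A plain change score has SD √(2(1 − ρ)) and power of 54%, 68%, 88% and 97% at ρ = 0.3, 0.5, 0.7 and 0.8. It gains only above ρ = 0.5 and loses below it, so the remedy is covariate adjustment rather than a change score.

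**A few large abnormalities.** Assume exactly 4 of 48 in the MMDT arm fall by 3 SD and all their values are kept.

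- Mean shift: 4 × 3 / 48 = 0.25 SD.
- The four outliers inflate the observed variance in that arm to about 1 + (4/48)(44/48) × 9 = 1.69, so the estimated standard error is √(1.69/48 + 1/48) = 0.237.
- The sampling SD of the difference, given four affected, is √(2/48) = 0.204.
- Raw t-test: z = (0.25 − 1.986 × 0.237) / 0.204 = −1.08, so detection in the harmful direction is about 14%.
- Adjusted at ρ = 0.7: the arm variances are 0.51 + 0.69 = 1.20 and 0.51, the estimated standard error is √(1.20/48 + 0.51/48) = 0.189, and the sampling SD is √(2 × 0.51/48) = 0.146. Then z = (0.25 − 1.986 × 0.189) / 0.146 = −0.86, so about 20%.
- If the four are absent, the remaining 44 have no shift and detection is the 2.5% error rate.

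A simulation of 20,000 trials gave 14%, 20% and 2.5%.

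**The case against.** **The plan is not in error.** A between-arm comparison of post-treatment values in a randomised trial is valid without baseline adjustment, and no stated figure is wrong. A condensed article may also leave shift tables, worst-value summaries and unscheduled samples to the full protocol or analysis plan. Both points stand, so the absence of those details is no finding. The by-visit t-test is different: the article states it, and an analysis plan that follows the article would inherit it.

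**Stronger readings that the text does not support.**

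- A reader might infer that abnormal values drop out of the comparison. That is a risk, not a stated result. Section 2.2 plans continued outcome measurement after withdrawal, though it does not say whether laboratory tests are included, and 2.11 requires an event to be both severe and related. AE incidence counts the event in any case.
- A reader might infer that LOCF replaces event values with earlier ones. LOCF appears only in the efficacy section, and ITT is defined there as a population, "all randomized participants who administered at least single dose of investigational product". Calling safety ITT therefore imports no imputation rule.
- A reader might infer that baseline is never used. The check on "whether there is a change beyond the normal range" implies some comparison within the participant. The supportable statement is that the t-tests make no stated use of baseline. Nor can one say that worsening of an already abnormal value goes uncounted, because the phrase is undefined.
- A reader might take the exclusion of patients with pseudoaldosteronism as a forecast of that harm. Section 2.2 only excludes people who have it.

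**Conclusion.** The point holds as a worthwhile improvement to a stated method, not as an invalid analysis.

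Two parts need no assumption about loss of data: between-arm tests at pre-treatment visits are uninformative, and unadjusted tests at Visits 3 and 4 give up precision whenever the baseline correlates with the later value. The size, 68% against 80% to 98%, rests on an assumed 0.5 SD shift and correlations of 0.5 to 0.8; the documents give neither.

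The third part is that visit means are a blunt tool for rare individual harm: about 14% detection with every event value kept and 20% with adjustment, assuming 4 of 48 affected by 3 SD and ρ = 0.7. The fall to 2.5% applies only if those participants have no value at that visit, which the protocol neither states nor rules out.

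**What to change.** Reword 2.12.2 before unblinding, to this effect:

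- For each continuous vital-sign and laboratory variable, compare the arms at Visits 3 and 4 by ANCOVA with the Visit 2 value as covariate.
- Show Visits 1 and 2 descriptively, with no between-arm test.
- Use observed values, and state that the LOCF rule of 2.12.1 does not apply to safety.
- Summarise by arm each participant's worst post-dose value, from whatever values were recorded, including any taken at withdrawal.

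Separately, 2.2 (serious adverse event) and 2.11 (severe and related) give different triggers for withdrawal. The two passages must be reconciled; this review takes no view on which rule is right.

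The cost is wording and slightly more analysis. The ANCOVA needs only values that 2.11 already records. The documents do not show that samples are taken at withdrawal, so the worst-value summary is limited to what exists. Worst values are more extreme than visit values in both arms, so they should be read as a contrast between arms and not against visit means.
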